## Abstract

Background/Objectives: Populations in Mediterranean countries are abandoning the traditional Mediterranean diet (MD) and lifestyle, shifting towards unhealthier habits due to profound cultural and socioeconomic changes. The SWITCHtoHEALTHY project aims to demonstrate the effectiveness of a multi-component nutritional intervention to improve the adherence of families to the MD in three Mediterranean countries, thus prompting a dietary behavior change. Methods: A parallel, randomized, single-blinded, and controlled multicentric nutritional intervention study will be conducted over 3 months in 480 families with children and adolescents aged 3–17 years from Spain, Morocco, and Turkey. The multi-component intervention will combine digital interactive tools, hands-on educational materials, and easy-to-eat healthy snacks developed for this study. Through the developed SWITCHtoHEALTHY app, families will receive personalized weekly meal plans, which also consider what children eat at school. The engagement of all family members will be prompted by using a life simulation game. In addition, a set of activities and educational materials for adolescents based on a learning-through-playing approach will be codesigned. Innovative and sustainable plant-based snacks will be developed and introduced into the children’s dietary plan as healthy alternatives for between meals. By using a full-factorial design, families will be randomized into eight groups (one control and seven interventions) to test the independent and combined effects of each component (application and/or educational materials and/or snacks). The impact of the intervention on diet quality, economy, and the environment, as well as on classical anthropometric parameters and vital signs, will be assessed in three different visits. The COM-B behavioral model will be used to assess essential factors driving the behavior change. The main outcome will be adherence to the MD assessed through MEDAS in adults and KIDMED in children and adolescents. Conclusions: SWITCHtoHEALTHY will provide new insights into the use of sustained models for inducing dietary and lifestyle behavior changes in the family setting. It will facilitate generating, boosting, and maintaining the switch to a healthier MD dietary pattern across the Mediterranean area. Registered Trial, National Institutes of Health, ClinicalTrials.gov (NCT06057324).

## 1. Introduction

Currently, unhealthy diets are recognized as one of the most important risk factors in the development of noncommunicable diseases (NCDs). According to the Global Burden of Disease study (GBD) 1990–2019 [1,2], the consumption of unhealthy foods and nutrients, including sugar-sweetened beverages, red meat, and sodium, is far higher than the optimal intake in young and middle-aged adults. Diet modernization has led to a shift from traditional dietary patterns to more convenient, processed, and less nutritious food choices, with negative health consequences like overweight, obesity, diabetes, elevated blood pressure, and hyperlipidemia, all metabolic risk factors for NCDs [3]. In 2023, more than 150 million people suffered from NCDs in the Eastern Mediterranean region, with cardiovascular diseases (CVDs) accounting for 17.9 million deaths [3]. These figures corroborate the increasingly evident abandonment of the Mediterranean traditional dietary pattern [4].

The Mediterranean diet (MD) is linked to a set of skills, knowledge, practices, and traditions ranging from cultivation to the processing, preparation, and particularly the consumption of food and defines a unique lifestyle recognized as a common cultural heritage of Mediterranean communities [5]. It is essentially a plant-based dietary pattern based on the consumption of high amounts of fresh fruits, vegetables, and legumes as the main sources of fiber and antioxidant compounds and cereals (mainly whole grain), nuts, and olive oil as the main sources of fat. It also includes an abundance of fish and shellfish and a moderate consumption of white meat, eggs, and dairy products (mainly yogurt and cheese) [6,7]. The MD is a sustainable food model that is recognized as (a) environmentally sustainable, protecting biodiversity; (b) culturally acceptable and fair; (c) economically accessible and affordable; and (d) nutritionally adequate, safe, and healthy, as represented in the new environmental dimension of the MD pyramid [7,8]. According to the results of a recent meta-review, higher MD adherence scores were significantly associated with a reduced risk of CVD, type 2 diabetes, overall cancer mortality, different cognitive diseases, fractures, and metabolic syndrome, in addition to lower body weight, BMI, and blood pressure [9]. The available literature regarding MD adherence in children and adolescents from Mediterranean countries shows a higher percentage of young people with low MD adherence than with high adherence, according to the KIDMED index [10,11]. These findings suggest that several factors are contributing to the erosion of traditional Mediterranean dietary habits, among which cultural, socioeconomic, and lifestyle changes have a primary role [12]. The abandonment of traditional eating habits, the high consumption of precooked food, the low consumption of fresh, local, and seasonal products, and a sedentary lifestyle denote profound social changes in the current food culture of the Mediterranean region, especially among younger generations [4,12]. All of this is aggravated by the decline in agricultural biodiversity, largely due to globalizing trends, climate change, and the mechanization of farming practices, which reduce the sustainability of local production systems and, with it, our ability to safeguard the Mediterranean diet [13].

Nevertheless, parental factors need to be considered, especially when it comes to barriers and facilitators for children’s dietary patterns. The family food environment becomes a strong predictor of children’s food preferences and eating behaviors. Parental food habits and feeding strategies are the most dominant determinants of a child’s food choices, which will persist throughout their life [14]. Some preliminary studies conducted with children and adolescents have found a significant positive correlation between MD adherence and family socioeconomic status, revealing that a higher MD adherence was associated with a better mother’s education and income level [11]. In addition, in the PASOS study recently conducted in 3607 children and adolescents in Spain, adherence to the MD was higher in children and adolescents with healthier parental lifestyle [15].

It is believed that the social context most likely to induce healthy behavior changes is the family [16]. The reciprocal adult–child relationship represents a way of influencing the behavior of both children and adults. Lasting dietary changes are more likely when they involve the family unit because of the increased likelihood that family members will act and sustain behaviors and because of the beneficial familial social support. However, the current evidence of interventions aimed at improving dietary habits by involving all the family is limited [17,18]. Most of these interventions are focused on the prevention or treatment of child obesity, evaluating the effectiveness of improving diet quality at home on classical health variables such as body composition, glucose, and lipid profiles [19,20,21]. But, as far as we know, there is no family-based intervention aimed at improving the adherence to MD. Although many interventions carried out in schools have been shown to be effective in promoting a healthier dietary pattern, it is not fully determined if these interventions result in changed behavior outside the school setting [17,22]. In fact, an intervention comparing a family-based, school-based, and combined approach demonstrated that changes in parenting practices and healthy dietary behaviors were achieved among those exposed to the family intervention [23].

Recent trends show an emerging number of technology-based or eHealth interventions to improve health outcomes for lifestyle behaviors, particularly in young populations [24,25,26,27]. However, there is poor evidence of the effectiveness of family-based nutrition education programs engaging parents and/or parents and their children directly using digital tools such as mobile apps [28]. Most of the existing mobile apps promoting the MD lack family-based dietary guidance in terms of food preferences, sociocultural aspects, and other family-related parameters. Moreover, there is a need for complementary nutrition interventions to build a supportive environment for effective healthy eating in the household [28,29,30]. Codifying the pros and cons of using digital tools in health/dietary interventions, we note as benefits the possibility for personalized and adaptive guidance, the interactive engagement of all family members, the facilitation of easy, consistent, and ongoing support, the encouragement of self-monitoring and reflection, and the facilitation of education through experimental learning; and, as drawbacks, we mention digital divide and accessibility issues, challenges related to sustained engagement over time, family digital dynamics and differences in motivation to use digital tools, complexity and usability issues, and, finally, challenges related to privacy and data security.

In this context, the SWITCHtoHEALTHY project aims to generate a dietary behavior change by demonstrating and reinforcing the role of the family in promoting a sustainable change towards enhancing adherence to the Mediterranean dietary pattern of all the family members (adults, adolescents, and children). To achieve this goal, a randomized, single-blinded, and controlled multicentric nutritional intervention study, involving families from three Mediterranean countries (Spain, Turkey, and Morocco), will be carried out. The study will test the effectiveness of a holistic family-based approach that combines. (1) digital interactive tools (SWITCHtoHEALTHY app) designed to support parents in preparing weekly healthier dietary plans for all the family members; (2) hands-on educational materials and activities designed through a learning-through-playing approach to increase adolescents’ knowledge and motivation on healthy and sustainable food habits; and (3) healthy and sustainable plant-based snacks to be introduced in children’s dietary plans to substitute less healthy options between meals. The plant-based snacks, digital tools (app and game), and educational materials will be developed based on their effectiveness in promoting adherence to the MD, addressing common barriers Mediterranean families face in adopting healthier dietary habits.

The intervention is grounded in the COM-B model, part of the Behavior Change Wheel (BCW) framework, focusing on capability, opportunity, and motivation as key drivers of behavior change. It integrates Social Cognitive Theory (SCT) principles, emphasizing family-based support and digital engagement through tools. This combination aims to support MD adherence by targeting individual knowledge, family reinforcement, and accessible resources [31].

A sustained enabling environment will be promoted throughout the project to increase the awareness of an MD-based healthy diet and lifestyle model across the Mediterranean region in eight participating countries (SWITCHtoHEALTHY project; https://switchtohealthy.eu/ (accessed on 3 June 2024)), namely Spain, Italy, Greece, Turkey, Lebanon, Egypt, Tunisia, and Morocco, involving different research institutions with complementary expertise and resources within the areas of nutrition, eHealth, digital technologies/ICT, agro-food, food eco-design, innovation, R&D&I, and food manufacturing.

## 2. Materials and Methods

### 2.1. Study Design and Setting

The SWITCHtoHEALTHY study is a parallel, randomized, single-blinded, and controlled multicentric nutritional intervention study. It aims to evaluate the effects of a multi-component intervention deployed at the family level, combining digital interactive tools and hands-on educational materials and activities with healthy and sustainable plant-based snacks, on the adherence to the MD pattern in 480 families with adolescents and children from three Mediterranean countries (Spain, Turkey, and Morocco), with 160 families per country. Secondarily, the effects of the multi-component intervention will be assessed according to lifestyle, anthropometric, dietary, sociodemographic, socioeconomic, and environmental indicators.

This study protocol was registered at ClinicalTrials.gov (NCT06057324) and is in accordance with the Helsinki Declaration and the Good Clinical Practice Guidelines on the International Conference of Harmonization. All the procedures described in the protocol, informed consent, and other documents have been reviewed and approved by the Ethics Committees of the three centers involved in the study: (1) Fundació Eurecat (study co-ordinator): Institut d’Investigació Sanitària Pere Virgili, IISPV (Ref. 135/2023); (2) Ethics Committee of Bursa Uludag University Faculty of Medicine Clinical Researches (Ref. 2023-23/29); and (3) Comité d’Ethique pour la Recherche Biomédicale (CERB), Université Mohammed V Faculté de Médecine et de Pharmacie de Rabat (preapproval). This protocol complies with the Standard Protocol Items: Recommendations for Clinical Trials (SPIRIT 2013 Statement and SPIRIT-AI extension) [32,33].

The 160 families recruited in each country will be randomly assigned into eight study groups (*n* = 20 families per group per country) according to a multi-component intervention including different combinations of the three study components (artificial intelligence (AI)-based app for all family; educational materials and empowerment activities for adolescents; and healthy plant-based snacks for children) and a control group that will receive basic Mediterranean guidelines for parents and their children (Figure 1).

To evaluate the overall effect of the intervention as well as the individual and combining effect of each intervention component, a full-factorial design will be used [34]. This design will allow us to evaluate the independent effect of the different intervention components versus the control group and, simultaneously, the summatory effect of combining different components on increasing the family adherence to the MD. This will therefore provide a stronger inference about the effect on the different implemented interventions [35].

The overall study duration will be 13 months for each participating family, including 3 main visits (V0, V1, and V2) (Figure 2). A prior preassessment visit will be performed at baseline, followed by the intervention study that will be deployed in the last 3 months (between month 10 and 13). According to this timeframe, this study will be arranged in two different phases (Figure 2).

*Phase 1* (*month 0 to month 9*): preassessment. The families will be recruited and included in this study; they will be randomly assigned to the different study groups; and consumption patterns and sociodemographic, socioeconomic, and environmental indicators will be evaluated through specific questionnaires. In addition, the different educational materials and activities, AI-based app, and healthy plant-based snacks will be developed prior to the start of the intervention study. This information will help us understand the context of each participant group and inform our analysis.

*Phase 2* (*month 10 to month 13*): the intervention study will be deployed at the family level. Families will receive the educational materials and activities, the AI-based app, and the plant-based snacks developed in Phase 1, depending on their assigned intervention group. In addition, anthropometrics, lifestyle, dietary, and socioeconomic and environmental indicators will be evaluated through specific questionnaires.

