### 2.7. Sample Size

The sample size was calculated based on differences in MD adherence score (primary outcome) measured by MEDAS and KIDMED questionnaires. The sample size was estimated using the analysis of variance (differences between 8 study groups). It was assumed that the alpha value would be equal to 0.05 and beta 0.20, exactly as reported in previous studies [61], with a common standard deviation equal to 1.19. The minimum group size needed to detect a minimum increase of 1 point in the intervention group’s MEDAS compared to the control group is equal to 45 families per study group (15 families per country). The total sample is, therefore, 45 × 8 = 360 families. However, assuming a 25% drop-out rate, the minimum group size is equal to 60 families per study group (20 families per country). Overall, 160 families will thus be recruited per country after obtaining the approval of the Ethics Committee of each recruiting center and written informed consent from parents and adolescents.

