### 2.10. Statistical Analysis

#### 2.10.1. Univariate Data Analysis

The data obtained from families in this study will be evaluated via an intention-to-treat (ITT) analysis, including data from families who drop out of the study, and per protocol (PP), that is, those families who have completed the treatment plan and who have exactly followed the instructions of the trial protocol. The error level of 0.05 will be set as a limit of statistical significance. A data analysis will be performed using the Statistical Software for Data Science (STATA, College Station, TX, USA) version 17.0 [63].

Mean and standard deviation will be reported for normally distributed variables and quantiles (25th percentile, median, and 75th percentile) for non-normally distributed variables. The Kolmogorov–Smirnov test and the Shapiro–Wilk test will be used to test for the normality of variables. The resulting scores of adherence to the MD (measured from the MEDAS and KIDMED questionnaires) will be used to calculate the mean differences between each intervention group and the control group before (V1) and after interventions (V2). Multiple comparisons (V2 vs. V0 and V2 vs. V1) of mean differences before and after interventions will be undertaken to assess the independent effect of interventions. The normality of the differences will be checked and, depending on the results, the following contrasts will be performed: parametric statistics (three-factor ANOVA with post hoc tests using the Bonferroni correction and considering the interactions between the following factors: app, educational materials, and snack products) will be used for normally distributed variables to compare differences in means and nonparametric statistics (Kruskal–Wallis test) will be used for non-normally distributed variables. Lineal regression and Spearman’s method will be used to test for correlations between normal and non-normal outcome variables, respectively.

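### The protocol does not say whether a component's effect is its factorial main effect or one group versus control, and its non-normal fallback drops the factorial model

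*Protocol article*

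**What the plan says.** Section 2.1 (Study Design and Setting) chooses a full-factorial design with eight groups formed from app, educational materials and snacks. It says the design will make it possible to "evaluate the independent effect of the different intervention components versus the control group and, simultaneously, the summatory effect of combining different components".

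Section 2.7 (Sample Size) uses the same kind of contrast. "The minimum group size needed to detect a minimum increase of 1 point in the intervention group" relative to control is given as 45 families, raised to 60 for 25% drop-out.

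Section 2.10.1 (Univariate Data Analysis) holds three relevant statements:
- The MEDAS and KIDMED scores are used to obtain "mean differences between each intervention group and the control group before (V1) and after interventions (V2").
- Multiple comparisons between visits (V2 with V0, V2 with V1) "will be undertaken to assess the independent effect of interventions".
- Depending on a normality check, the test is a "three-factor ANOVA with post hoc tests using the Bonferroni correction and considering the interactions between the following factors: app, educational materials, and snack products"; otherwise "nonparametric statistics (Kruskal–Wallis test) will be used for non-normally distributed variables".

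**The concern.** In a 2×2×2 factorial, the effect of a component is normally its main effect: the four groups that receive it against the four that do not. Every family contributes. The alternative is a simple effect, which compares the group with that component alone against control. The two differ in precision, and they differ in meaning when components interact.

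The article points to both. The design, sample-size and effect-calculation sentences speak of group versus control, while the parametric test is the factorial model. Because neither is named as the component effect, two analysts could follow the text and report different primary answers for the app, for education and for snacks. Under the Kruskal–Wallis branch only the group-versus-control differences remain.

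The same gap affects combinations. Section 2.1 promises a summed effect of combining components without defining it. If it is taken as combination minus control, a group can look good only because one of its components works. This matters for use of the results: Section 2.5 wants to scale up the most effective interventions, and the Discussion wants the most impactful components proposed for health programmes.

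**Working it through.** **Inputs.** SD 1.19, alpha 0.05, power 80%, difference 1 point, 45 completers and 60 randomised families per group (Section 2.7); eight equal groups (Section 2.6). Assumptions: two-sided tests, normal approximation, and one score per family with SD 1.19, as in Section 2.7.

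**1. The plan's own figure.** n per group = 2 × (z₁ + z₂)² × SD² / difference², with z₂ = 0.842 for 80% power.
- Unadjusted, z₁ = 1.960: 2 × 2.802² × 1.416 = 22.2, so 23.
- Bonferroni over the 7 comparisons with control, z₁ = 2.690: 35.3, so 36.
- Bonferroni over all 28 pairs of eight groups, z₁ = 3.124: 44.5, so 45.

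The last matches the stated 45. The article does not say that this was the method, so it is an inference. Drop-out: 45 / 0.75 = 60 per group, and 8 × 60 = 480. The stated size is reproduced.

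**2. Families in each contrast.**
- Single-component group versus control: 60 + 60 = 120 of 480, or 25%.
- Main effect: 240 versus 240, all 480.

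**3. Precision with 45 completers per group.**
- One group versus control: SE = 1.19 × √(2/45) = 0.251.
- Main effect, 180 versus 180: SE = 1.19 × √(2/180) = 0.125.
- The variance ratio is 180/45 = 4.

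**4. Difference detectable with 80% power.**
- Two-sided 0.05: 2.802 × 0.251 = 0.70 points for one group versus control; 2.802 × 0.1254 = 0.35 for a main effect.
- Main effects with Bonferroni over three: (2.394 + 0.842) × 0.1254 = 0.41.

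**5. Power at equal alpha.** For an illustrative true effect of 0.5 points (my value; the plan targets 1 point):

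| Two-sided alpha | Group versus control | Main effect |
|---|---|---|
| 0.05 | 51% | 98% |
| 0.05/7 | 24% | 90% |

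For the plan's 1 point at 0.05/28, group versus control has 81% power and a main effect nearly 100%.

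**6. What a combination minus control measures.** If components add, app + snacks minus control = app effect + snack effect. A positive result does not show that snacks contribute. In a simulation of 5,000 trials (45 per group, app worth 1 point, the other two worth nothing), each of the three app combinations beat control in about 90% at 0.05/7. The main effects of education and snacks were significant in 5.4% and 4.4% at 0.05, which is the nominal rate.

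**7. Precision of the interactions.** A two-way interaction is a difference of differences among four means of 90 families: SE = 1.19 × √(4/90) = 0.251, detectable 0.70 points. The three-way contrast has SE = 1.19 × √(8/45) = 0.502, detectable 2.802 × 0.502 = 1.41 points.

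**8. Could the non-normal branch be reached?** The scores are sums of whole-point items (Section 2.5). I assumed individual change scores that are normal but rounded to whole points. Shapiro–Wilk at 0.05 then rejects in 98% of samples of 45 at SD 1.19, 19% at SD 2.5, and every sample of 360 at either SD. Family averages would be rejected less often. The branch is a realistic prospect, but how likely depends on the unit and sample tested.

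**The case against.** The strongest reply is that the factorial analysis is already planned. Section 2.10.1 names a three-factor ANOVA with the three components as factors and their interactions, directly after the sentence on the independent effect. Its main effects use every family. This stands, and it rules out a reading that a reader might infer: that the plan replaces main effects with group-versus-control contrasts and leaves three quarters of the families unused. That fraction describes one single-component contrast, not the planned ANOVA.

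Other parts of the reply also stand:
- The sentence containing "will be undertaken to assess the independent effect of interventions" has visit comparisons as its subject. It does not say that the seven control contrasts define the independent effect.
- The Bonferroni post hoc tests are not limited to control. If they cover all pairs, app + snacks against app alone is among them, and that does test the added component. Inert components would therefore not necessarily be carried forward.
- The 90% in step 6 is not an error rate. If the app works, app + snacks truly beats control. The fault would lie in attributing that result to snacks.
- Group-versus-control differences are legitimate when packages may interact, and ranking estimates is often left to an analysis plan.

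The reply does not remove the inconsistency. Three sections word or calculate the effect against control, and no sentence makes the ANOVA main effect the answer. The Kruskal–Wallis branch is fixed in the text rather than left open, and it cannot supply main effects or interactions.

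**Conclusion.** The point holds as an inconsistency in what is being estimated, together with a fallback test that does not fit the design. It should be corrected. If the group-versus-control wording is followed, each single-component estimate has four times the variance of the main effect, its detectable difference doubles from 0.35 to 0.70 points, and no combination-versus-control difference isolates an added component. If the ANOVA main effects are followed, none of this loss occurs.

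A reader might also infer that the trial is wrongly sized. It is not: 45 per group is adequate for the plan's 1-point pairwise difference even at 0.05/28, and more than adequate for main effects.

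The figures assume one score per family, SD 1.19, two-sided tests and 45 completers in every group. A main effect equals the effect of a component given alone only if interactions are small.

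**What to change.** 1. In Sections 2.1 and 2.10.1, state that the independent effect of the app, of education and of snacks is each one's main effect in the three-factor model: four groups with it versus four without it.
2. State that combining is judged by the interaction contrasts, that is, whether a combination gains more or less than the sum of its components.
3. Make the seven group-versus-control differences secondary, and show them beside the main effects if an interaction is large.
4. Replace Kruskal–Wallis by the same three-factor model with, for example, robust or bootstrap standard errors when scores are non-normal.
5. In Section 2.7, keep 45 and 60 per group. The detectable main effect can be added: 0.35 points unadjusted, 0.41 with Bonferroni over three main effects.

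The cost is wording: no new data and no more families. There are two downsides. A main effect averages over the presence and absence of the other components, which item 3 covers. Two-way interactions are estimated only as precisely as a single group-versus-control difference (SE 0.251), so a non-significant interaction should not be read as proof that components simply add.
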